The secondary outcome measures are:Ambulation speed, step length and cadence during the ambulation test over 10 m (AT10) barefoot at comfortable speed without technical aid, and step length and cadence during AT10 at maximal speed [61];Ambulation speed, step length, cadence and physiological cost index over a 2-min ambulation test at maximal speed without technical aid [72];Subjective self-assessment of perceived function (DAS) indicating the degree of functional incapacity evaluated by the patient for hygiene and dressing activities, pain and cosmesis [70, 73];Global test of functional dependency (Barthel Index) [74];Quality of life (SF 36) [75, 76];Anxiety and depression test (Geriatric Depression Scale, GDS) [77];Evaluation by questionnaires, completed by the patient (and/or a third person), on the weekly frequency and duration of the conventional rehabilitation sessions and the amount of professional help received at home during the study period, to estimate the direct costs from the point of view of the health coverage system;Estimation of the total cost of healthcare, including medical, socio-medical, allowance cost, combining the points of view of the medical insurance and of the State, to encompass all paying institutions;Evaluation of the amount of self-rehabilitation in the GSC group, through the filling ratio of diaries over 12 months [28], (www.i-gsc.com);Evaluation of functioning and home adaptation by an occupational therapist and by questionnaires, in a sub-group of 44 participants in two of the six study centers;Evaluation of the psychological adjustment of the patient, by a study psychologist in the same sub-group of 44 participants in two of the six study centers, to assess the required psychological resources and the need for psychological support. Each of these participants will be contacted for a first visit and offered to consult with the psychologist for the two-year study period. The frequency of encounters will be adjusted to the need of each patient.

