### Setting and recruitment

This multicenter trial involves six French centers (the medical centers in Saint-Etienne, Reims, Bordeaux, Toulouse, and Henri Mondor and Lariboisière university hospitals in Paris). Each of these centers admits > 100 cases/year of patients with moderate to severe stroke-induced hemiparesis for specialized rehabilitation and will recruit 20 to 24 patients. A 3-year time-frame is planned for the study, each center starting the study once the total expected number of participants to be enrolled are lined up. The objective is thus to run the protocol simultaneously for all participants of each center, to make optimal use of the study therapist’s time (GSC group).

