#### Analysis of the randomized study

The analysis of the randomized study will be carried out based on intent to treat and per protocol.

The primary and secondary criteria and their changes from M6 to M18 will be compared between the two groups using mixed models. The changes will also be compared at M24, i.e. 6 months following the end of the study treatment. These same analyzes will be carried out by subgroups, comparing the availability of a psychological follow-up or not, ie in the participants recruited by the Mondor-Lariboisière centers versus those of the other centers.

A multivariable analysis will be carried out by considering the characteristics of the patients (age, sex), the center, the initial severity parameters of the disease (sensory disturbances) or time since stroke, as well as the availability or not of a psychologist.

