#### Pre−/post-analysis

With patients being their own control, the changes in various functional parameters during the first 6 months of follow-up with conventional therapy (from Day 1 to M6) will be compared with the changes in these same parameters:during the randomized study between M6 and M12during the randomized study between M12 and M18and during follow-up between M18 and M24.

The mean changes and the rate of progression over periods of 6 months will be compared. These same comparisons will be realized in subgroups according to the randomization group, but also depending on any specific psychotherapeutic management (for 44 participants, in the two centers involved).

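### Psychologist availability is fixed by centre, so the multivariable analysis that also lists centre cannot isolate its effect, and the planned psychologist split compares two hospitals with four

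*Protocol article*

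**What the plan says.** The trial has six centres ("This multicenter trial involves six French centers"), and each "will recruit 20 to 24 patients" (Setting and recruitment). Under Outcome measures, psychological adjustment is assessed "by a study psychologist in the same sub-group of 44 participants in two of the six study centers". That section adds: "Each of these participants will be contacted for a first visit and offered to consult with the psychologist for the two-year study period". The occupational-therapy evaluation is confined to the same 44 patients.

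Analysis of the randomized study does two things with this feature:

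- It plans the primary and secondary comparisons by subgroup according to psychological follow-up, and explains the split as "ie in the participants recruited by the Mondor-Lariboisière centers versus those of the other centers".
- It plans a multivariable analysis whose factors are age, sex, centre, initial severity, "or time since stroke, as well as the availability or not of a psychologist".

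Pre−/post-analysis repeats the split, "depending on any specific psychotherapeutic management (for 44 participants, in the two centers involved"). Randomisation is to GSC or CONV, stratified by centre. Access to the psychologist is not randomised.

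**The concern.** A covariate that takes one value for everyone in a centre carries no information beyond the centre itself. If a single model holds both centre and availability, the availability term either has no estimate or becomes a comparison of two hospitals with four. The subgroup analysis and the pre/post split share the second difficulty. The two sets of hospitals may differ in case mix. They also differ in the GSC physiotherapist, since one is funded per centre, and possibly in calendar time, since each centre starts once its own cohort is lined up. The occupational-therapy assessment goes to the same 44 patients, so even two otherwise identical sets of hospitals would not separate the psychologist from that assessment. What is at stake is how a secondary result is read: the analysis as listed could yield a figure named after the psychologist that the design cannot tie to the psychologist.

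**Working it through.** **1. Does the subgroup coincide with two whole centres?** Two centres at 20 to 24 patients give 2 × 20 = 40 to 2 × 24 = 48. The stated 44 equals 2 × 22 and fits full enrolment at both. The subgroup definition by recruiting centre, and the offer of the psychologist to every one of the 44, point the same way. So, for each patient,

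availability = I(Mondor) + I(Lariboisière),

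which is an exact sum of centre indicators.

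**2. Rank with centre as a fixed effect.** Layout: N = 124, centre sizes 22, 22, 20, 20, 20, 20 (an assumption that sums to 124), 1:1 allocation within centre, and simulated patient covariates. The aliasing follows from the identity in step 1 and does not depend on these choices. The base terms are intercept, arm, age, sex, sensory disturbance and time since stroke.

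| Terms added to the base | Columns | Rank |
|---|---|---|
| 5 centre indicators | 11 | 11 |
| 5 centre indicators + availability | 12 | 11 |
| availability only, no centre | 7 | 7 |
| 5 centre indicators + availability × arm | 12 | 12 |
| 5 centre indicators + centre × arm + availability × arm | 17 | 16 |

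With centre in the model, the availability main effect adds no rank. Without centre it can be fitted, but it is then only the contrast of two centres with four. The availability-by-arm interaction is estimable beside centre main effects, unless centre-by-arm terms are also present.

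**3. Centre as a random effect.** Availability is then a centre-level covariate with 6 − 2 = 4 degrees of freedom between centres. The critical t is 2.78, against 1.98 on 122 degrees of freedom. There are C(6,2) = 15 ways to choose two of six centres, so the smallest two-sided exact permutation p-value is 1/15 = 0.067. With outcome variance scaled to 1 and intraclass correlation ρ,

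Var = ρ/2 + (1 − ρ)/44 + ρ/4 + (1 − ρ)/80.

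The documents give no ρ. Over an assumed range of 0.01 to 0.10:

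- The difference detectable with 80% power is 0.77 to 1.23 SD. If centre is ignored it appears to be 0.53 SD.
- Ignoring centre would raise the type I error of this contrast from a nominal 5% to about 7% to 26%.

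**4. Precision of the estimable quantity, the treatment-by-centre-group interaction on the MFS.** With 44 patients in two centres and 124 − 44 = 80 in four, 1:1 allocation gives 22 and 40 per arm.

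SE = SD × √(2/22 + 2/40) = SD × 0.3754.

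The planning effect in Sample size is 4.4 × (0.30 − 0.10) = 0.88 points. Power for an interaction of that size is Φ(0.88/SE − 1.96).

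| Assumed SD of change | SE | 95% half-width | Power for 0.88 |
|---|---|---|---|
| 1.9 | 0.713 | 1.40 | 23% |
| 1.0 | 0.375 | 0.74 | 65% |

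The 1.9 in Sample size is the spread of a single score. It equals the SD of change only if the within-patient correlation is 0.5, because SD of change = 1.9 × √(2(1 − r)). The 1.0 is purely an assumption.

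**The case against.** Several points on the other side stand.

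- **Centre is not fixed as a fixed effect.** The article speaks of mixed models for the randomised comparison and does not say how centre enters. With random centres availability has an estimate. A reader might infer that the effect can never be computed; that is true only with fixed centres.
- **The factor list may be a list of candidates.** It is introduced loosely and contains an *or*. Still, nothing in the text keeps centre and availability apart, and an analysis that takes the list as written inherits the problem.
- **The centre basis of the split is disclosed.** The section itself explains the subgroup as two named centres against the rest. A reader might infer that the sponsor plans to claim a causal psychologist effect, but no passage says so and Objectives lists no such aim. What remains is that the comparison is named by psychological follow-up while its content is hospitals.
- **Assessor differences are a weak argument for the co-primary outcomes.** One central blinded rater scores the MFS at all visits, and maximal speed is re-scored blind from video.
- **Separate significance tests in each subgroup are not established.** The wording is compatible with an interaction comparison.
- **Low interaction power is common to subgroup analyses and varies with assumptions.** With baseline adjustment and an assumed correlation of 0.9, the residual SD is 1.9 × √(1 − 0.81) = 0.83, the half-width 0.61 and the power 81%. The 23% is one point in a range, and precision is not the defect itself.

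None of this makes the availability main effect separable from the other differences between the two sets of centres.

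**Conclusion.** The point holds as a limit on one secondary covariate and two secondary splits. With fixed centre effects the availability main effect is fully aliased (rank 11 with or without it). With random centre effects it rests on 2 versus 4 centre means, about 4 degrees of freedom, and stays confounded with the GSC therapist, case mix and the occupational-therapy assessment. This needs only that availability is constant within centre, which the article's own subgroup definition provides. It does not depend on any SD or intraclass correlation.

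A reader might infer that the main result is compromised. It is not: aliasing of this term leaves the fitted values and the GSC-versus-CONV coefficient unchanged, and both co-primary comparisons and the stratified randomisation are untouched. Nor can the interaction be called hopeless on the documents alone, because they do not give the SD of change. At an SD of 1.9 the interval is wider on each side than the 0.88-point planning effect (1.40); at 1.0 it is narrower (0.74).

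**What to change.** Keep centre in the multivariable model and remove the availability main effect. Report the subgroup analysis in Analysis of the randomized study as one treatment-by-centre-group interaction with its 95% confidence interval, marked exploratory. Do not enter centre-by-arm terms in that model, since they would alias the interaction as well. Label this estimate, and the matching split in Pre−/post-analysis, as Mondor-Lariboisière versus other centres rather than as an effect of the psychologist, and note that the same 44 patients also receive the occupational-therapy assessment.

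The cost is a change of wording and a small change to one secondary analysis. No new data are needed and the primary analysis stays as it is. The sponsor gives up a psychologist effect that the design cannot isolate.

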#### Pre−/post-analysis

With patients being their own control, the changes in various functional parameters during the first 6 months of follow-up with conventional therapy (from Day 1 to M6) will be compared with the changes in these same parameters:during the randomized study between M6 and M12during the randomized study between M12 and M18and during follow-up between M18 and M24.

The mean changes and the rate of progression over periods of 6 months will be compared. These same comparisons will be realized in subgroups according to the randomization group, but also depending on any specific psychotherapeutic management (for 44 participants, in the two centers involved).

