### Research design

Neurorestore is a prospective, controlled, randomized, multicenter, single-blind study on 124 participants with chronic spastic hemiparesis (> 1 year post stroke) in six French tertiary rehabilitation centers. For all participants, the study will begin with an initial 6-month follow up phase with conventional therapy, to assess its socio-economic costs and the stabilization of the clinical status of stroke patients at a chronic stage in the current rehabilitation system (Fig. 1). The second phase will be the randomized and comparative phase, assessing Guided Self-Rehabilitation Contract (GSC) versus conventional therapy (CONV) alone, over 1 year. It is important to note that in the GSC group, participants will be free of continuing whichever additional treatment they wish, including conventional therapy as prescribed by their physicians. At the end of this comparative period, each participant will be followed for a second, final 6 month follow-up phase with conventional therapy, exactly as in the initial phase. This final phase will explore the persistence of possible differences between the two groups. The total duration of study participation for each subject is 2 years. Data will be analyzed based on intention-to-treat and per-protocol analyses.

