Endurance 2-min walking test – Physiological Cost Index	x	x	x	x	x
Modified Frenchay Scale	x	x	x	x	x
Disability Assessment Scale (DAS)	x	x	x	x	x
Barthel Index	x	x	x	x	x
Quality of Life scale (SF36)	x	x	x	x	x
Geriatric Depression Scale	x	x	x	x	x
Questionnaires to patient/caregiver on frequen cy of therapy sessions	x	x	x	x	x
Occupational therapy assessment (in subgroup of 44 patients)		x		x	
Clinical psychologist assessment (in subgroup of 44 patients)	x	x		x	

Throughout the study, participants will be permitted to freely use any “antispastic” medication such as systemic synaptic depressor drugs (baclofen, benzodiazepines, dantrolene sodium, tizanidine) or botulinum toxin injections as well as any technical aid deemed necessary to their attending physician or physiotherapist. However, it is recommended to taper systemic antispastic agents as much as possible (or taper them off) during the first 6-month follow-up phase because of their well-documented antiplasticity and anti-recovery effects [78–81]. If participants are still under systemic depressors at the onset of the randomized study phase, doses should then be kept constant as much as possible.

After the first 6 months of follow-up, participants will be randomized into two groups: “conventional therapy” (CONV) and “Guided Self-rehabilitation Contract” (GSC) (see Randomization).

In order to minimize any nocebo effect in the conventional treatment group, the referent coordinator will not disclose the details of the Guided Self-rehabilitation Contract to the physicians and physiotherapists who treat participants in the CONV group, nor to the CONV participants themselves.

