#### Statistical analysis

This study will require several statistical analyzes. The main analysis will focus on the randomized phase of the study (from M6 to M18).

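### The supplementary pre/post analysis uses D1–M6 as each patient's control and repeats the comparison within arms, but that phase has its own drug policy, so within-arm differences cannot be attributed to GSC

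*Protocol article*

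**What the plan says.** All references are to the protocol article.

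- **Pre-/post-analysis.** The reference is the change from Day 1 to M6: "With patients being their own control, the changes in various functional parameters during the first 6 months of follow-up with conventional therapy". It is compared with the changes in M6–M12, M12–M18 and M18–M24. The section then adds: "These same comparisons will be realized in subgroups according to the randomization group", and does the same by psychotherapeutic management. It states no contrast of GSC against CONV for these period differences.
- **Research design.** The first phase is presented as six months of conventional therapy, meant "to assess its socio-economic costs and the stabilization of the clinical status of stroke patients at a chronic stage".
- **Procedures.** In that same phase, "it is recommended to taper systemic antispastic agents as much as possible (or taper them off) during the first 6-month follow-up phase", and the reason given is "because of their well-documented antiplasticity and anti-recovery effects". For patients still on these drugs when the randomised phase starts, "doses should then be kept constant as much as possible".
- **Statistical analysis and Analysis of the randomized study.** The main analysis is the randomised phase. There, the primary and secondary criteria and "their changes from M6 to M18 will be compared between the two groups using mixed models". Changes are also compared at M24.

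**The concern.** An own-control comparison is informative only if the control period differs from the later period in the treatment under study and in little else. Here the first phase also carries a recommended withdrawal of drugs that the protocol says hinder recovery, while the randomised phase carries a recommendation to hold doses steady. Repeat-test effects may differ between periods as well.

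Within one arm, these influences cannot be separated from GSC. The CONV arm goes through the same first phase and the same visits, so it could remove whatever is shared, but this analysis does not use it for that purpose. Two misreadings are possible: an apparent acceleration in the GSC arm that CONV shares, or a real GSC effect hidden because the reference period was itself lifted by the taper. Setting a significant result in one arm beside a non-significant one in the other does not repair this, because it is not a test of the difference between arms.

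**Working it through.** The plan gives no sample size, power or alpha for the pre/post analysis, so there is no figure of its own to reproduce. The check has two parts.

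**1. The passages side by side**

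| Period | Rehabilitation | Recommendation on systemic antispastics |
|---|---|---|
| D1–M6 (control) | Conventional, all patients | Taper as far as possible |
| M6–M18 | GSC plus any conventional therapy, or conventional alone | Doses constant as far as possible |

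In the GSC arm, the change of rehabilitation and the change of drug policy both fall at M6. In the CONV arm only the drug policy changes. The difference between arms isolates GSC, provided the period effect is the same in both; neither arm alone does.

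**2. Illustration of what a shared period shift does to the within-arm test**

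Inputs from Sample size: MFS SD 1.9 and 62 patients per group. Assumed, with no source in the documents: correlation r between any two visits of 0.8 to 0.9, two-sided 5% for this test, a shift of 0.3 MFS points common to both arms, and no GSC effect.

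The comparison of M6–M12 with D1–M6 is (M12 − M6) − (M6 − D1) = M12 − 2·M6 + D1. With equal correlation its variance is (1 + 4 + 1)(1 − r)SD² = 6(1 − r)SD².

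| | r = 0.8 | r = 0.9 |
|---|---|---|
| Variance | 6 × 0.2 × 3.61 = 4.332 | 6 × 0.1 × 3.61 = 2.166 |
| SD | 2.08 | 1.47 |
| SE = SD/√62 | 0.264 | 0.187 |
| 0.3/SE | 1.135 | 1.605 |
| Rejection, normal | 21% | 36% |
| Rejection, t-test | 20% | 35% |

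So the range is about 20–36% instead of 5%. The comparison of M12–M18 with D1–M6 involves four distinct visits; its variance is 4(1 − r)SD², and the same shift gives 28–50%.

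With the adjacent-period rates, the chance that GSC is significant and CONV is not, with no GSC effect, is 0.206 × 0.794 = 16% to 0.361 × 0.639 = 23%.

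**Opposite direction.** If the shift favours D1–M6 by 0.3 points, a real GSC acceleration of 0.3 points has an expected within-arm contrast of 0.3 − 0.3 = 0, and the test rejects only 5% of the time.

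**Steady trend.** If patients change by a constant g per six months, the contrast is g − g = 0. Only effects that differ between periods matter.

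**Between-arm contrast.** A shift equal in both arms cancels and the test stays at 5%. Its SE is √2 times the within-arm SE: 0.374 (r = 0.8) or 0.264 (r = 0.9).

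**The case against.** The case for leaving the plan as it is has force on several points.

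- **The concurrent comparison already exists.** Efficacy is judged by the between-group mixed models for M6–M18, and persistence by the comparison at M24. Both arms reach M6 after the same first phase. This stands. A reader might infer that the taper undermines the main result; the documents do not support that.
- **No efficacy claim is attached.** The section says that changes are compared and gives no alpha or decision rule. The paired tests listed under Statistical tests and software used are introduced for subgroups defined by starting or demographic variables. It also reports both arms, so a similar CONV change would be visible. This lowers the stakes. Still, the section is not labelled descriptive, unlike the analysis of the first phase, and seeing both arms is not the same as contrasting them.
- **The taper is limited.** It is a recommendation, concerns only patients on systemic agents (a proportion not given), and is openly stated. This stands, and is why no size can be given.
- **Phase 1 may not be misdescribed.** Conventional therapy can be read as the rehabilitation regimen, with medication left free. That is a fair reading, so this is a point to reconcile rather than a flat contradiction. It does not make the drug policy the same across periods.
- **False positives are not the likelier error.** Withdrawing drugs said to impede recovery would raise the D1–M6 change, and early learning on repeated tests would do the same. Both work against GSC. This stands. A reader might take the 20–36% as the expected error; it shows one direction under an assumed shift.

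It is also tempting to take the 10% CONV improvement in Sample size as the period shift. That figure is an assumed improvement in the CONV group, not a difference between two six-month changes, and steady improvement would cancel.

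**Conclusion.** The point holds, within limits. As written, the pre/post analysis cannot attribute a within-arm difference between periods to GSC, because the drug recommendation changes at M6 together with the treatment and no between-arm contrast is stated. Direction and size of the bias are both open; by the protocol's own rationale, masking is the more likely result if the taper works as intended. The illustrative 20–36% rests on a shift and correlations that the documents do not supply. This is a defect in a supplementary analysis that is worth correcting, and it does not reach the primary comparison.

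**What to change.** 1. In Pre-/post-analysis, label the overall and within-arm period comparisons as descriptive.
2. Base any statement about treatment on the arm-by-period contrast: the change in M6–M12, M12–M18 or M18–M24 minus the change in D1–M6, GSC versus CONV, from one mixed model over the five visits. Report it alongside the planned M6–M18 and M24 comparisons.
3. Report Phase 1 change separately for patients whose systemic antispastic treatment did and did not change between D1 and M6. Table 1 already schedules a treatment inventory at every visit. This split is not randomised and should be read as description.
4. Reconcile the account of Phase 1 in Research design and Pre-/post-analysis with the taper recommendation in Procedures. No change to treatment is asked for.

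The cost is wording in the analysis plan and no new data. The between-arm contrast has a wider confidence interval, by a factor of √2 ≈ 1.41 with equal arms: in the illustration, a half-width of 1.96 × 0.374 = 0.73 points against 1.96 × 0.264 = 0.52 at r = 0.8.
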